# Optimized vs. Standard Automated Peritoneal Dialysis Regimens (OptiStAR): study protocol for a randomized controlled crossover trial

**DOI:** 10.1186/s40814-020-00620-2

**Published:** 2020-06-10

**Keywords:** Renal replacement therapy, Automated peritoneal dialysis, Glucose absorption, Metabolic cost

## Abstract

**Background:**

It has been estimated that automated peritoneal dialysis (APD) is currently the fastest growing renal replacement therapy in the world. However, in light of the growing number of diabetic patients on peritoneal dialysis (PD), the unwanted glucose absorption during APD remains problematic. Recent results, using an extended 3-pore model of APD, indicated that large reductions in glucose absorption are possible by using optimized bi-modal treatment regimens, having “UF cycles” using a higher glucose concentration, and “Clearance cycles” using a low concentration or, preferentially, no glucose. The present study is designed to test the theoretical prediction of a lower glucose absorption using these novel regimes.

**Methods:**

This study is a randomized single-center, open-label, prospective study. Prevalent PD patients between 18 and 75 years old without known catheter problems or recent peritonitis are eligible for inclusion. Patients are allocated to a first treatment session of either standard APD (6 × 2 L 1.36% over 9 h) or optimized APD (7 × 2 L 2.27% + 5 × 2 L 0.1% over 8 h). A second treatment session using the other treatment will be performed in a crossover fashion. Samples of the dialysis fluid will be taken before and after the treatment, and the volume of the dialysate before and after the treatment will be carefully assessed. The primary endpoint is difference in glucose absorption between the optimized and standard treatment. Secondary endpoints are ultrafiltration, sodium removal, Kt/V urea, and Kt/V Creatinine. The study will be closed when a total of 20 patients have successfully completed the interventions or terminated according to interim analysis. A Monte Carlo power analysis shows that the study has 80% power to detect a difference of 10 g (in line with that of theoretical results) in glucose absorption between the two treatments in 10 patients.

**Discussion:**

The present study is the first clinical investigation of optimized bi-modal treatments proposed by recent theoretical studies.

**Trial registration:**

ClinicalTrials.gov identifier: NCT04017572. Registration date: July 12, 2019, retrospectively registered.

## Background

In peritoneal dialysis (PD), the peritoneum of the patient is used as a biological dialyzer membrane by filling and draining the peritoneal cavity with dialysis fluid at pre-determined time points. Excess water is removed from the patient by osmosis, which is usually induced by the presence of high concentrations of glucose in the dialysate. The patient absorbs a significant amount of this glucose. In the light of the growing number of diabetic patients on PD, this unwanted glucose absorption is problematic and often represents a clinical challenge. A recent meta-analysis indicated that around 50% of PD patients may develop a glucose disorder which can significantly increase mortality [1].

Automated peritoneal dialysis is PD performed with the aid of a machine, a cycler, which aids the patient or the caregiver from the tedious work of filling and draining the PD fluid. Novel cyclers allow the treatment to be varied in a multitude of ways and recently, it was shown, using a theoretical model, that automated peritoneal dialysis could be improved by using a modified “bi-modal” treatment regimen in which exchanges using no osmotic agent is alternated with short “UF exchanges” having an osmotic agent [2]. Especially, it was shown that the potentially harmful glucose absorption could be reduced by 20–30%. Thus, the potential benefits of the novel regimens appear to be substantial.

The current pilot study aims to evaluate the clinical safety and feasibility of such optimized regimens in a small study using the HomeChoice Pro cycler. Since HomeChoice does not support exchanges having different lengths, the treatment will be divided into a “UF-part” comprising all the UF cycles and a “Clearance part”. A nurse will supervise the treatment and switch between the two parts manually. Moreover, as 0% glucose PD fluid is not available, a 0.1% glucose hemodialysis (CRRT) fluid will be used. We will use 2.27% glucose (Dianeal) for the UF exchanges.

## Method

### Hypothesis

We will test the hypothesis that there is a 10-g difference in terms of glucose absorption, between a standard APD (6 × 2 L 1.36% over 9 h) regime and an optimized APD regimen (7 × 2 L 2.27% + 5 × 2 L 0.1% over ~ 8 h) while there are no differences in osmotic water transport (“UF”), sodium removal, Kt/V creatinine, or Kt/V urea between the regimens.

### Study design

We will be conducting a randomized single-center, investigator-initiated, prospective, open-label study of two different APD regimens. The study is approved by the regional ethical vetting board in Córdoba, Argentina (Health ministry document registry number 3788), and will be conducted at the Hospital Privado Universitario in Córdoba. Overviews of the trial design according to the Standard Protocol Items: Recommendations for Interventional Trials (SPIRIT) statement and an overview of patient flow through the study are presented in Table 1 and Fig. 1, respectively. A SPIRIT checklist is provided in a supplemental file. A member of the research team will obtain informed consent non-consecutively from eligible participants. The length of the study will be from signing of informed consent until 30 days after the start of the first treatment session. A study investigator will follow all patients in a visit at the trial center. All patients will be evaluated with regard to potential adverse effects by one of the investigators.

**Table 1 Tab1:** Overview of enrolment, interventions, and assessments according to the SPIRIT (Standard Protocol Items: Recommendations for Interventional Trials) statement

	Study period							
	Recruitment	Allocation	Post-allocation					Close-out
Time point	−t_1_	0	t_1_	t_2_	t_3_	t_4_	t_5_	t_6_
Recruitment								
► Eligibility	**x**							
► Informed consent	**x**							
► Allocation		**x**						
Interventions								
► Optimized APD				**x**	**x**			
► Standard APD				**x**	**x**			
Assessments								
► 4 h D/P creatinine		**x**						
► Urea DV		**x**						
► Glucose absorption				**x**	**x**			
► UF and NaR				**x**	**x**			
► Blood chemistry			**x**	**x**	**x**	**x**		
► Physical examination			**x**	**x**	**x**	**x**	**x**	
► Kt/V urea+crea				**x**	**x**			
► Adverse events				**x**	**x**	**x**	**x**	**x**

*DV* distribution volume, *D/P* dialysate-over-plasma concentration ratio, *UF* net drained volume, *NaR* sodium removal, *Kt/V* calculated from net urea removal divided by plasma urea concentration and DV

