### Study interventions

Patients starting with a standard APD regimen will receive treatment with 12 L of dialysis fluid (Dianeal 1.36% glucose) over 9 h (see Fig. 2a). The patient will then, within 4 weeks (1 − 28 days), receive an optimized APD regimen using 7 × 2 L of 2.27% Dianeal during 280 min followed by 5 × 2 L 0.1% glucose fluid (Certesol 0/3.5, Rivero) during 200 min (see Fig. 2b) (lactate-based fluid for continuous hemodialysis/hemodiafiltration). The dwell times for the optimized regimes should theoretically be varied depending on the transport type, but for simplicity, the dwell times have been set fixed in accordance with the above treatment times. This means that the total time under treatment will be approximately 8 h for the optimized regime. Patients will be in the supine position throughout the study protocol session time. Samples of dialysate will be collected from all drained bags (including the initial rinse), immediately after instillation of the first cycle and directly after instillation of the post-treatment rinse dwell.

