### Secondary outcomes

Secondary outcomes are osmotic water transport (“UF”), sodium removal, Kt/V urea, Kt/V creatinine, and incidence of complications up to 14 days post-intervention.

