### Analysis of outcomes

Study outcomes will be analyzed using a Wilcoxon rank-sum test. A non-parametric test was chosen since such tests are more robust to outliers, which can have undue influence on the results of a parametric test for a small number of patients. In the event of no difference between the groups with regard to secondary outcomes and a difference in the primary outcome (glucose absorption lower in the optimized group), we will interpret such results as supporting our hypothesis but that confirmatory studies are needed using a higher number of patients since the low *N* in the current study may not be adequately powered to detect differences in the secondary outcomes. In this situation, a Monte Carlo-based sensitivity analysis will be performed to quantify the minimal difference needed to yield a significant difference in the secondary outcomes.

In the case of both a significant difference between the groups with regard to secondary outcomes and in the primary outcome (with glucose absorption lower in the optimized group), we will interpret these results as supportive of our hypothesis if the difference in secondary outcomes implies an improvement. Indeed, due to stirring effects, the higher DFR associated with the optimized regimes may result in improved NaR, urea, and creatinine clearance and UF [2]. In any other case, the differences will be compared to the differences expected theoretically according to the extended 3-pore model [2].

Should the primary outcome be negative or show a higher glucose absorption for the optimized regimen, then, all other outcomes are regarded as exploratory, with the exception of number of complications, and no emphasis will be placed on any differences between the treatment groups.

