### Harms

The investigators will evaluate all patients with regard to potential adverse events (AEs) or serious adverse events (SAEs). All potential AEs and SAEs are recorded in the CRF. We define a SAE as an event during the study period that fulfills one or more of the following criteria: results in death, is life-threatening, requires prolongation of hospitalization, results in persistent or significant disability or incapacitation, or any other important medical event. The principal investigators are responsible for the treatment of AEs or SAEs until resolution. Depending on the nature of the AE or SAE, treatment may take place on-site, at the local hospital, or as an outpatient. Principal investigator is responsible for reporting AEs to the institutional review board, participating investigators, and applicable regulatory authorities, Argentine Medical Products Agency (ANMAT), as required per regulations with an expedited copy sent simultaneously to Baxter. All SAEs/significant safety concerns will be sent to Baxter within 24 h. If the principal investigator deems the SAE as being related to the technical equipment or the fluids used, this will be promptly reported to the sponsor, which has the responsibility to report to the Argentine Medical Products Agency (ANMAT) and the local and regional ethical vetting board.

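### The 14-day complication window is not secured after the second session: it runs past the end of the study when the sessions are 17 to 28 days apart

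*Protocol article*

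**What the plan says.** Three places in the protocol article fix the timing.

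- **Secondary outcomes** includes the "incidence of complications up to 14 days post-intervention".
- **Study interventions** sets the interval between sessions: "The patient will then, within 4 weeks (1 − 28 days), receive an optimized APD regimen". The interval is written for patients who start with the standard regimen. None is written for the reverse order.
- **Study design** sets the end of the study: "The length of the study will be from signing of informed consent until 30 days after the start of the first treatment session". The clock starts at the first session, not the second.

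The abstract confirms that each patient has both sessions: "A second treatment session using the other treatment will be performed in a crossover fashion". Three further passages bear on how much the outcome matters. Background states that "The current pilot study aims to evaluate the clinical safety and feasibility of such optimized regimens". Analysis of outcomes says that if the primary outcome fails, "all other outcomes are regarded as exploratory, with the exception of number of complications". Harms ties serious events to the same period: "We define a SAE as an event during the study period that fulfills one or more of the following criteria".

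**The concern.** The end of the study is counted from the first session, while the second session may come almost four weeks later. A 14-day window that opens late in that interval cannot close before day 30. The protocol therefore defines an outcome that its own follow-up does not always cover.

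The stake is safety information. Complications are the one secondary outcome that is not set aside if the primary outcome fails, and safety is a stated aim of this pilot. With a target of 20 patients, a few unrecorded events could change the picture. A serious event after day 30 would also fall outside the protocol's own definition, because that definition is limited to the study period. The loss is one-sided within a patient: the window after the first session is never cut by the end of the study, and only the window after the second can be.

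**Working it through.** The protocol gives no calculation of its own on this point, so there is no figure to reproduce. The check is day arithmetic.

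**Inputs**

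- Complication window: 14 days (Secondary outcomes).
- Gap between sessions, g: 1 to 28 days (Study interventions), assumed the same for both orders.
- End of study: day 30, counting the first session as day 0 (Study design).

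**Formulas**

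- Days remaining after the second session = 30 − g.
- Days of its window observed = the smaller of 14 and 30 − g.
- The window is cut short when 30 − g < 14, that is, when g > 16.
- The second session falls inside the first session's window when g < 14.

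| Gap g (days) | Days remaining after second session | Observed of the 14 | Second session inside first window? |
|---|---|---|---|
| 1 | 29 | 14 | yes |
| 13 | 17 | 14 | yes |
| 14 | 16 | 14 | no |
| 16 | 14 | 14 | no |
| 17 | 13 | 13 | no |
| 21 | 9 | 9 | no |
| 28 | 2 | 2 | no |

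**Results**

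- Gaps 17 to 28: 28 − 17 + 1 = 12 of the 28 permitted values cut the second window short.
- Gaps 1 to 16: 16 of the 28 values leave the second window complete. In 13 of these (gaps 1 to 13) the windows overlap. In 3 (gaps 14, 15 and 16) both windows are complete and separate.
- Largest shortfall: a second session on day 28 needs follow-up to 28 + 14 = day 42, which is 42 − 30 = 12 days past the stated end.

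**Other readings of the window.** If it is meant to run only after the last session, the same 12 gaps are cut short. If it is meant to run only after the first session, it always fits within 30 days, but the second regimen then has no window of its own. Neither reading gives every patient 14 observed days after the second session.

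**The case against.** **Follow-up after the second session is planned.** Table 1 places adverse-event assessments at t4, t5 and t6, after the sessions at t2 and t3. This is true, and it shows the intent. But the table as shown carries no calendar days, and the enrolment and allocation flowchart (Fig. 1) is not available here. Nothing in the text moves the end of the study beyond day 30.

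**Randomized order balances the loss.** On average it does spread the shortened windows over both regimens. It does not recover events that are never recorded.

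**Attribution belongs in an analysis plan.** This stands. At gaps of 1 to 13 days both windows fit within the 30 days, so nothing is lost to observation. What is open is the regimen to which an event in the shared days is assigned. An analysis plan or full protocol not shown here may settle that, and no two sections contradict each other on it. A reader might add the 13 overlapping gaps to the 12 shortened ones and conclude that the outcome fails for 25 of the 28 gaps. That sum mixes an attribution question with a conflict between sections, and only the 12 are the conflict.

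**The outcome is not stated per regimen.** Secondary outcomes does not say so. A comparison by regimen is a fair inference from Analysis of outcomes, which exempts complications from the rule that no weight is placed on differences between treatment groups. The shortfall after a late second session does not depend on that inference.

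**Conclusion.** The concern holds in a limited form. For gaps of 17 to 28 days the stated end of the study cuts the 14-day window after the second session, to 13 days at the shortest of these gaps and to 2 days at the longest. An analysis plan cannot repair this, because those days are not observed.

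Two stronger readings are not supported. A reader might infer that the outcome cannot be observed for each regimen, but gaps of 14 to 16 days give two complete, separate windows. A reader might also infer that the second regimen's window is always cut short, but it is complete for gaps of 1 to 16 days.

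The conclusion rests on three assumptions: days are counted from the day of each session, the 1-to-28-day interval applies to both orders, and day 30 ends the recording of complications. The figure of 12 in 28 counts permitted gaps. The document gives no distribution of actual gaps, so the proportion of patients affected is unknown and could be none. The primary outcome, the sample size and the secondary outcomes measured at the sessions are untouched.

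**What to change.** Reconcile Study design, Study interventions and Secondary outcomes by defining the end of complication follow-up as no earlier than 14 days after the second session, whichever regimen comes second. The study period used in Harms to define serious events should have the same end, so that the two definitions agree.

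If complications are to be compared by regimen, the analysis plan should say how an event is attributed when the windows overlap. That is a clarification and not part of the contradiction.

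The cost is a change of wording and at most 12 more days of adverse-event follow-up (day 42 instead of day 30) for a patient whose second session is on day 28. Patients with gaps of up to 16 days need no extension. No change to the sample size or the primary analysis is needed.

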**Fig. 1 Fig1:**
[figure not shown]
Detailed enrollment and allocation flowchart for the Optimized vs. Standard APD regimens (OptiStAR) study

### Study participants and pre-intervention assessment

All patients will be selected from the outpatient renal clinic at the Hospital Privado Universitario in Córdoba, Argentina. Participants who provide written informed consent and who meet all of the inclusion and none of the exclusion criteria will be eligible for this study. After allocation, the patient will visit the clinic for screening, and a physical examination will be performed, and a blood samples will be collected. Prior to enrollment, the patient will perform a 4-h dwell using 2.27% glucose, and the dialysate-to-plasma (D/P) concentration ratio of creatinine will be determined. The urea distribution volume (V) will be estimated using the Watson equation.

### Pre-allocation inclusion and exclusion criteria

Inclusion criteria are age between 18 and 75 years, duration of PD (automated peritoneal dialysis (APD), or continuous ambulatory peritoneal dialysis (CAPD)) > 4 weeks.

Exclusion criteria are severe heart failure (New York Heart Association Functional Classification; NYHA III or IV), pregnancy, catheter malfunction, or peritonitis within 3 months prior to the trial.

### Post-allocation exclusion criteria

After allocation, patients may be excluded due to in-trial peritonitis, catheter malfunction, inability to successfully complete both APD regimens, or the clinical judgment of the treating physician not to include the patient.

### Intra- and post-interventional care of the patients

Eligible patients who have given consent to participate in the study will receive routine care. The interventions will start in the morning, and the patient will come to the clinic. After an initial rinse with 1.36% glucose, each patient thereafter receives either a standard or optimized APD in-clinic. After the treatment, a rinse will be performed using 1.36% glucose.

### Randomization and blinding

Consenting patients that fulfill the inclusion criteria and meet no exclusion criteria will be randomized by the investigators using a random number generator to start treatment with either the standard APD or optimized APD regime. A priori we expect no difference in who receives which treatment first. Allocation concealment will be performed using a sealed opaque envelope.

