### Sample size and power analysis

Published relative standard error values for glucose absorption comprise values ranging from 10 to 30% with a mean of 18% [3]. The worst performance for the optimized regime is a reduction in glucose absorption of about 10 g. Thus, a Monte Carlo-based power analysis was performed by the generation of 10,000 random samples *S* and *O* of size *N* from two normal sampling distributions having *μ* = 44 g; *σ* = 7.74 and *μ* = 34 g; *σ* = 5.94. The theoretically expected difference will differ depending on transport type and is higher with a faster peritoneal membrane. A Wilcoxon rank-sum test was performed to assess the statistical difference between the samples *S* and *O*. The statistical power was calculated as the number of significant (*P* < 0.05) results, for example, 8687/10,000 implies a statistical power of ~ 87%. The procedure was repeated by step-wise increasing *N* until a statistical power of > 80% was attained, which occurred at *N* = 10. For *N* = 20, the statistical power was found to be > 98%.

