### Statistical analysis plan

The study will continue until a total of 20 patients have been included. This number is higher than that estimated in the power analysis. However, only patients who successfully completed both treatment regimens will be included in the analysis. Due to the complicated technical nature of the experimental setup, there may be a significant amount of unusable results, and the relative over-recruitment is aimed at compensating for a high post-allocation exclusion rate. The investigating team will perform the statistical analyses. In general, (1) analysis will be performed on a per-protocol basis, (2) all hypothesis tests will be paired and two-sided, with a maximal type I error risk of 0.05 ,and (3) imputation will not be used to correct for missing data in the analysis.

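### The order of the regimens is randomized, but the fixed analysis has no period term, so a period effect, if there is one, would cost power and, given an uneven split, shift the contrast

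*Protocol article*

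**What the plan says.** The abstract sets out a two-session crossover: "A second treatment session using the other treatment will be performed in a crossover fashion". Under Study interventions, the sessions are 1 to 28 days apart.

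Under Randomization and blinding, patients are "randomized by the investigators using a random number generator to start treatment with either the standard APD or optimized APD regime", with sealed opaque envelopes. No block size or fixed ratio of sequences is given. The section adds: "A priori we expect no difference in who receives which treatment first". I read this as expecting no order effect; it gives no figure.

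Under Statistical analysis plan, "all hypothesis tests will be paired and two-sided, with a maximal type I error risk of 0.05", the analysis is per protocol, and only patients who complete both regimens count. That section expects many exclusions after allocation. Under Analysis of outcomes, "Study outcomes will be analyzed using a Wilcoxon rank-sum test". Neither section uses period or sequence. The power calculation draws independent samples from "two normal sampling distributions having *μ* = 44 g; *σ* = 7.74 and *μ* = 34 g; *σ* = 5.94", with no period component.

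**The concern.** Randomizing the order protects the regimen comparison from a systematic order effect, and the sequence label allows a period effect to be removed. The plan does the first and leaves the second unused.

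If absorption tends to differ between first and second sessions, two things follow. First, patients who start on standard and patients who start on optimized have within-patient differences displaced in opposite directions. A paired test that ignores period treats this spread as noise. Second, if the sequences are unequal among completers, the displacements do not cancel and part of the period effect stays in the estimate. Balance at allocation does not guarantee balance among completers.

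A period effect is conceivable. CAPD patients are eligible and may be new to a cycler, the nurse switches between the two parts by hand, and the outcome depends on weighed bags. The documents offer no evidence for or against it. At stake are the precision of the primary contrast and how the one realised split is read.

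**Working it through.** **Inputs from the protocol article.** Means 44 g and 34 g, difference 10 g; SDs 7.74 and 5.94; 20 patients planned, 10 as the number judged sufficient for power; two-sided 0.05.

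**Assumptions (not in the documents).** Period effect π (session 2 minus session 1) of 0, 2, 5 or 10 g; within-patient correlation 0 or 0.5; unrestricted 1:1 allocation where a split is random. Because the plan calls its tests paired, the unadjusted analysis is taken as the signed-rank test.

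**1. The plan's own power.** Simulating two independent normal samples with the rank-sum test gives 76.4% at N = 9, 83.2% at N = 10 and 99.0% at N = 20. The stated figures (above 80% first at N = 10, above 98% at N = 20) reproduce.

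**2. SD of the within-patient difference.** With correlation 0: √(7.74² + 5.94²) = √95.19 = 9.76 g. With correlation 0.5: √(95.19 − 7.74 × 5.94) = √49.22 = 7.02 g.

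**3. Effect on the contrast.** Let D be standard minus optimized and τ the true difference. D has mean τ − π in patients who start on standard and τ + π in those who start on optimized. The unadjusted mean of D is therefore τ − π(n1 − n2)/n, where n1 patients start on standard.
- At 14:6 the shift is 5 × 8/20 = 2.0 g for π = 5 g, against a target of 10 g.
- At 10:10 it is zero.
- Over the randomization n1 − n2 averages zero, so the estimate is unbiased.

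**4. Effect on the error variance.** With equal sequences the unadjusted variance of D is SD² + π². For π = 5 g: √(95.19 + 25) = 10.96 g instead of 9.76 g.

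**5. Chance of an uneven split under unrestricted allocation (binomial).** Exact balance: 24.6% with 10 completers, 17.6% with 20. A split of 7:3 or worse with 10: 34.4%. A split of 14:6 or worse with 20: 11.5%.

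**6. Power for 10 g, correlation 0 (simulation).**

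| Period effect | Signed-rank, random split, 10 completers | Signed-rank, random split, 20 completers |
|---|---|---|
| 0 g | 80% | 99% |
| 2 g | 79% | 98% |
| 5 g | 71% | 96% |
| 10 g | 49% | 83% |

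A period-adjusted t analysis with balanced sequences has about 81% (10 completers) and 99% (20) in every row. With correlation 0.5 and π = 5 g, the comparison is 89% against 97% with 10 completers, and 99.8% against about 100% with 20.

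**7. Which part causes the loss.** With 10 completers and π = 5 g, power is 71% with a random split, 72% with exact balance and no period term, and 81% with balance and a period term. Nearly all the loss comes from omitting period.

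**8. Conditional and overall behaviour, π = 5 g, correlation 0.** Given a 70/30 split, signed-rank power is 53% (10 completers) or 88% (20) when the imbalance works against the regimen effect, and 87% or 99.8% when it works with it. Type I error given that split is about 6% (10) and 10% (20). Over the randomization it stays near 5%.

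**9. Cost of adjusting when there is no period effect.** The adjusted standard error is (SD/2)√(1/n1 + 1/n2). At equal sequences this equals SD/√n, so only one degree of freedom is lost. At 70/30 it is larger by 1/√(4 × 0.7 × 0.3) = 1.09. The noncentral t distribution then gives about 74% power at 7:3 and 98% at 14:6.

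**The case against.** The case against is substantial.

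- **Allocation.** A random number generator can produce permuted blocks as easily as an unrestricted list, and a journal article commonly leaves block details to the full protocol. A reader might infer simple randomization, but the text does not say so, and the split probabilities above hold only if it was used. This stands; the test without a period term is the firmer point.
- **Bias and type I error.** A reader might infer that the planned comparison is biased, or that its type I error is well above 5%. The documents do not support this. Both statements hold only given an uneven split and an assumed period effect. Over the randomization there is no bias and the paired test holds its level. Nor is chance imbalance the main source of lost power (step 7).
- **Existence of a period effect.** None is documented and the plan expects none. Sessions are single, supervised and fixed in volume and dwell time. Staff learning runs mostly across patients, not between one patient's two sessions. An effect of 5 g would be half the target difference. This stands, so the point is conditional.
- **Choice of remedy.** Using the rank-sum test on period differences as the main analysis would cost power where the trial is weakest. At 5:5 with SD 9.76 g it has 69% against 79% for the signed-rank test when there is no period effect, and it is still about 3 points behind when the effect is 5 g. This also stands, and it decides the form of the fix.

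None of this supplies a reason to leave the randomized sequence out of the analysis.

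**Conclusion.** The point holds in conditional form. The plan randomizes order and then fixes an analysis of completers that cannot separate a period effect from error or, under an uneven split, from the regimen contrast. Whether this matters depends on a period effect that the documents neither show nor exclude.

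If it were 5 g, the power cost at the planned 10 g difference would be about 3 points with 20 completers (99% to 96%) and about 10 points with 10 (81% to 71%), at a difference SD of 9.76 g and correlation 0. In a realised 14:6 split the estimate would move by 2 g. With a 2 g effect the power cost is 1 to 2 points. The matter is modest if all 20 complete; it carries more weight if exclusions leave about 10 completers, or at the interim look at 10. It does not undermine the validity of the randomized comparison.

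**What to change.** 1. If not already arranged, allocate the remaining patients so that the two sequences stay equal, for example in permuted blocks. State the method, and report the sequence split among completers.
2. Pre-specify a period-adjusted regimen difference with its confidence interval, from a linear model of each patient's standard-minus-optimized difference on sequence. With sequence coded +1 and −1, the intercept is the mean of the two sequence means, and the period effect drops out of it.
3. Add, as a supportive analysis, the rank-sum comparison of period 1 minus period 2 differences between the two sequences. This gives the named test a valid crossover use and keeps the robustness to outliers that the plan wants. It should not be the main test. Besides its lower power at 5:5, its smallest exact two-sided P there is 2/252 = 0.0079, so it could never meet the interim efficacy boundary of P ≤ 0.001.

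Blocking is free and no new data are needed. With balanced sequences the model costs one degree of freedom: at no period effect its power matches the signed-rank test (about 80% against 79% at 5:5, 99% for both at 10:10). With uneven sequences and no period effect it loses some power: about 74% against 80% at 7:3, and 98% against 99% at 14:6.
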